## Abstract

**Background:**

Food insecurity, poor nutrition, and diet-related diseases create major intersecting health challenges. The Veterans Health Administration (VHA) has identified food insecurity as a high-priority problem and established regular clinical screening. Veterans with identified food insecurity and diet-sensitive cardiometabolic health conditions will benefit from the successful implementation of effective Food is Medicine interventions.

**Methods:**

This pragmatic, quasi-experimental intervention study of effectiveness and implementation of a produce-prescription program is conducted in 2 VA hospital health systems in Salt Lake City, Utah, and Houston, Texas. Eligible Veterans have (a) a diet-sensitive cardiometabolic health condition (obesity, hypertension, and/or diabetes) identified in the electronic health record (EHR) by diagnostic codes (ICD-10) and/or lab values and (b) low-income identified by priority status in administrative data. Program enrollment is pragmatically integrated within the VA clinical care process of food security screening and service referrals. Eligible Veterans who screen positive for food insecurity during clinical care processes are referred to the intervention. The Veterans Affairs FreshConnect Produce Prescription (VA FCPRx) intervention program includes 12 months of a produce prescription allowance for purchasing fresh fruits or vegetables, provided as $100 monthly on a pre-paid card for use at local grocery stores. The program also includes culinary education through cooking courses provided by VA nutritionists or nutritional consults provided one-on-one by a VA dietitian. Process and outcome measures will be evaluated using the PRISM RE-AIM framework. Health outcomes related to diet-sensitive chronic conditions (e.g., HbA1c levels for patients with diabetes) and healthcare costs (e.g., outpatient costs) are assessed using EHR data. VA FCPRx participant outcomes are assessed in comparison to a group of similar Veterans using intention-to-treat analyses. Patient-reported outcomes, implementation strategies and outcomes, and staff and Veteran experience are assessed with a combination of surveys, focus groups, and program administrative data.

**Discussion:**

This pragmatic quasi-experimental intervention study will provide important new evidence about the impact of a produce prescription program for U.S. Veterans on health outcomes, healthcare costs, and patient-reported outcomes. The assessment of effectiveness and implementation processes and outcomes will inform the design and scaling of impactful, pragmatic, cost-effective programs for food insecure Veterans with diet-sensitive cardiometabolic conditions.

**Supplementary Information:**

The online version contains supplementary material available at 10.1186/s12889-025-23355-2.

## Background

Food insecurity is the lack of consistent, readily available, and safe food and affects approximately 17 million Americans, or 12.8% of the population [1, 2]. In addition to a sufficient quantity of food, ‘nutrition security’, or access to adequate quantities of food of appropriate nutritional value, is increasingly complementing the concept of food security, as it emphasizes dietary quality beyond caloric sufficiency [3, 4]. Food insecurity is a major threat to health and well-being [5–9]. The nutritional quality of the food is a crucial mediator of health outcomes. Food insecurity and poor nutrition are associated with an increased risk for multiple chronic diet-sensitive health conditions, including diabetes and related metabolic disturbances, obesity, hypertension, and cardiovascular disease [10]. A growing body of research has outlined the extent to which food or nutrition insecurity can impede diabetes management, [11–13] present as a barrier to treating obesity, [14, 15] and disproportionately influence cardiovascular outcomes. [16] Food insecurity is interlinked with other complex social needs [17, 18].

“Food is Medicine” or “Healthcare by Food” interventions to address food and nutrition insecurity, social needs, and health employ broad strategies to address complex challenges [19–22]. Food is Medicine interventions target specific diet-sensitive health conditions and social needs [21]. The goals of these interventions are to attenuate the impact of food insecurity, improve nutrition, help address economic social needs, and improve health and health inequities in at-risk populations [23]. Specific Food is Medicine intervention strategies include providing healthful food directly from healthcare organizations with curated food boxes or medically-tailored meals [24] or produce prescriptions to purchase fruits and vegetables [25]. These interventions have the potential to be cost-effective or even cost-saving for healthcare systems, given the far-reaching impacts of food insecurity and poor diet quality [26].

Thus far, produce prescriptions have been studied less often than other Food is Medicine strategies [27]. A systematic review and meta-analysis examining pre/post cardiometabolic outcomes in produce prescription recipients across 13 different studies demonstrated reductions in body mass index (BMI) and hemoglobin A1c (HbA1c) and improvements in eating behaviors, such as food and vegetable intake [28]. Results from randomized trials have demonstrated mixed findings for HbA1c impact in produce prescription participants with diabetes compared to controls [29]. The variability in these findings may relate to heterogeneity of produce prescription program designs, implementation approaches, and patient populations. Studies that include education components, such as provision of recipes and cooking courses (often referred to as culinary education) have a higher potential for health impact [19, 21, 28, 30]. A large review of studies that included a culinary education component demonstrated increases in fruit and vegetable intake, and suggested beneficial changes in HbA1c and BMI [31]. Of note, studies to date have generally been relatively small and many are 6 months or less in duration.

U.S. Veterans are vulnerable to experiencing food insecurity with prevalence estimates ranging from 6 to 22% [6–9]. Survey estimates for sub-populations of Veterans during the COVID-19 pandemic were even higher, above 30% [32, 33]. Poor diet can also exacerbate mental health conditions. The burden of chronic illness and mental health conditions can each affect income and earning potential, influence spending tradeoffs, and promote even poorer eating habits, creating a feedback loop of stress and poor health [34]. The Veterans Health Administration (VHA) began a large-scale program screening Veterans for food security during healthcare encounters in 2017 [35], providing an ideal avenue for identifying potential participants for a pragmatic study. This study is large, multi-site, focused uniquely on Veterans, conducted within the largest integrated healthcare system in the U.S., uses a grocery-focused produce prescription intervention, and incorporates Electronic Health Record (EHR) based outcomes. This combination of factors is being addressed for the first time in this study.

### Aims

The aims of this protocol are to describe the VA Fresh Connect Produce Prescription Program (VA FCPRx), a pragmatic, quasi-experimental study designed to assess the impact of a produce prescription program 12 months in duration on Veterans with food insecurity and specific diet-sensitive cardiometabolic conditions. In this protocol, we describe the effectiveness study and characterize implementation and process measures for VA FCPRx including program enrollment processes, participation, satisfaction, and implementation strategies.

## Methods

### Study design

Veterans experiencing or at risk for food insecurity, diagnosed with a cardiometabolic diet sensitive condition including hypertension, obesity, and/or diabetes, and a comparison group of similar Veterans will be enrolled in VA FCPRx to estimate the effect of produce prescription on clinical measures, healthcare utilization, and self-reported behavior and well-being.

Primary outcomes: Clinical measures, including body mass index (BMI), blood pressure, and metabolic control (HbA1c) derived from the VA EHR.

Secondary outcomes: Healthcare utilization, including primary care visits, pharmacy utilization, inpatient admissions, and ED visits. Veteran-reported health outcomes, including subjective ratings of health.

Exploratory outcomes: Veteran-reported consumption of fruits and vegetables, nutrition security, depression symptoms, and other well-being indices.

We will also assess implementation processes and outcomes.

### Setting

The study is conducted at VA Salt Lake City and VA Houston Medical Centers. These VA facilities were chosen based on prior pilot food security interventions successfully implemented at these sites.

### Program oversight and ethics review

Given the partnerships between the evaluation study team (centered at the University of Utah), the funder (The Rockefeller Foundation), the non-profit organization providing the produce incentives (About Fresh), and the VHA, there was a need for a governance structure to guide implementation activities and data agreements. An Innovation Cooperative Research and Development Agreement (CRADA) governing information sharing, and funds management was completed to enable program implementation, processes, and evaluation across multiple institutions. The University of Utah Institutional Review Board and Salt Lake City VA Research and Development Committee reviewed and approved all evaluation study procedures.

### Eligibility and screening

Eligible participants are identified using VA EHR data from among currently active patients defined by a visit to a participating VA medical center within the preceding 12 months. Inclusion criteria are:

1) An indicator in the VA EHR for economic hardship (Designated membership in VA benefits criteria priority groups 5 or 7, based on Veteran benefits. These groups indicate a Veteran who has low-income without a service-connected disability).

2) One or more diet-sensitive cardiometabolic condition a) hypertension, b) obesity, or c) type 2 diabetes or malnutrition related diabetes. Cardiometabolic condition is determined by diagnostic code within the VA EHR (International Classification of Disease, ICD-10) or by laboratory values. Table 1 shows the specific EHR ICD-10 codes and laboratory values. Consent is not required for this screening or identification process.

**Table 1 Tab1:**
[figure not shown]
ICD-10 codes and laboratory values used to identify diet-sensitive conditions

### Intervention enrollment process (Screening)

Veterans who meet eligibility criteria are identified by a monthly VA EHR review by the evaluation team. Intervention enrollment will total at least 500 (250 per site). Enrollment will be closed once enrollment targets are reached. This was derived based on a power analysis performed on the primary outcomes coupled with practical considerations relating to the largest number of Veterans for whom the intervention and supportive health services would be available (see outcomes variables section for power analysis information). Of note, a recent systematic review of produce prescription programs included studies with adult sample sizes ranging from 21–243, thus, our planned sample of 500 is relatively large for the field to date [36]. Enrollment in the intervention group will continue until the planned sample size (*n* = 500) is reached.

A roster of eligible participants is made available on a secure Microsoft SharePoint site. This site is accessible only to the evaluation team and authorized nutritionists, dietitians, and social workers providing care to food-insecure Veterans. This screening approach supports the pragmatic enrollment process in this study. A Veteran who screens positive for food insecurity during clinical care is then referred to a social worker or dietitian. Social workers and dietitians at each study site are instructed to review the roster and offer FCPRx to Veterans who qualify (see Fig. 1). Veterans sign a release of information to permit information sharing with the Produce Prescription team. Figure 1 shows the study selection flow.

### VA FCPRx program

#### Produce prescription benefit

The produce prescription benefit is provided by the non-profit organization About Fresh^© ^ [42]. Enrolled Veterans receive a pre-paid card with a monthly allowance of $100 for 12 months, which can be used at participating grocery stores to purchase fresh fruits and vegetables. Each month’s prescription benefit must be used during the month of issuance and does not “roll over” into subsequent months. Participating Veterans receive a combination of live phone and text support from About Fresh for any challenges with card usage. Participating grocery stores include large, national, and locally based stores throughout Texas, Utah, and surrounding states, such as Albertson’s, Kroger/Smith’s, and Wal-Mart [43].

#### Culinary education

Along with the monetary benefit of the program, participants will receive education designed to help them integrate the purchased produce into their diet, with a participant choice of: (1) a supportive nutrition class delivered in VA called Healthy Teaching Kitchen, offered virtually once per week for 4 weeks or (2) one-on-one consultation with a VA dietitian.

#### Comparison group participants

The comparison group for our study will consist of Veterans who meet eligibility criteria at study sites (e.g., screening and cardiometabolic conditions) but did not participate in the intervention. It is anticipated that this group will be enrolled after the intervention group has reached capacity. This comparison group was chosen based on likely demographic similarity and the study goal for a pragmatic rather than a randomized design focus on a program embedded in VA clinical care. There are multiple potential reasons Veterans might qualify for inclusion but not enroll in VAFCPRx, including not being offered enrollment by clinical staff during the pragmatic clinic enrollment process or because they decline to participate.

#### Implementation and effectiveness outcomes

The VA FCRPRx study metrics are based on the Practical Implementation Sustainability Model (PRISM) and related Reach, Effectiveness, Adoption, Implementation, and Maintenance (RE-AIM) framework to assess outcomes and implementation [44]. Comparisons of health and healthcare cost outcomes derived from VA EHR data, including BMI and pharmacy utilization. Implementation metrics were selected to inform scalable implementation at additional future VA sites and future sustainment of the program.

Specific metrics, measurement strategies, and analytic approach are outlined in Table 2.

**Table 2 Tab2:**
[figure not shown]
Metrics Overview Based on PRISM-REAIM

Program enrollees and the subsample of comparison group Veterans are invited to complete a survey three times during the study: at baseline shortly after enrollment, 6 months after enrollment, and 12 months after enrollment. Potential survey participants (anticipated *n* = 1000) are mailed an opt-out letter for the survey. If they do not opt out within 3 weeks, they are sent a survey to complete using the online platform Qualtrics, with the first page containing a consent document (survey completion implies consent) [45]. Each survey includes structured measures including the food security screening questions used in VA care known as the Hunger Vital Sign™ [46], a nutrition measure including reports of fruit and vegetable intake (National Cancer Institute Dietary Screener Questionnaire), [47], a validated single-item self-reported health scale [48], and assessments of anxiety and depression, among other measures [49] (see Table 3 for complete list of survey measures). After completion of each individual survey, enrollees will receive a $10 gift card. After completing all three surveys, enrollees will have received a total of $30 in gift cards.

**Table 3 Tab3:** Survey Components and Time Points

Concept	Measurement Tool	Group	Time Point
Food Security	Household Food Security questionnaire [50, 51]	Tx and Comparison	1, 2, 3
Food Security Screening	Office of Food Security VA Food Insecurity Self Screening questionnaire [52]	Tx and Comparison	1, 2, 3
Nutrition Security Screening	2-item Nutrition Security Screener (NSS) [53]	Tx and Comparison	1, 2, 3
Nutrition Insecurity	Modified: National Cancer Institute’s Dietary Screener Questionnaire [47]	Tx and Comparison	1, 2, 3
Self-rated Health	Self-health-related quality of life Survey [48]	Tx and Comparison	1, 2, 3
Food Cost	Cost and Quality Questionnaire [54]	Tx and Comparison	1, 2, 3
Well-Being	Well-Being Signs Measurement [55]	Tx and Comparison	1, 2, 3
Well-Being	The World Health Organization- Five Well-Being Index (WHO-5) [56]	Tx and Comparison	1, 2, 3
Depression	Patient Health Questionnaire [49]	Tx	1, 2, 3
Anxiety	Generalized Anxiety Disorder Screen (GAD-7) [57]	Tx	1, 2, 3
Benefit Usage	About Fresh Card Usage Questionnaire	Tx	1, 2, 3
Patient Satisfaction with VA Care	Experience of Care Measures (VA Survey of Healthcare Experiences of Patients (SHEP) [58]	Tx and Comparison	1, 2, 3
VA FCPRx Satisfaction	Program Satisfaction Questionnaire [59]	Tx	1, 2, 3
Program Recommendation	Net Promoter Score [60]	Tx	1, 2, 3

### Data management

EHR-based demographic, health, and healthcare utilization data are stored within the VA Informatics Network Computing Infrastructure (VINCI), a secure VA computing environment. [61] Survey data from the Qualtrics survey are stored on secure University of Utah servers. Data relating to produce prescription card usage (allocated funds used per month, shopping trips per month, store locations) are transferred from Fresh Connect to the study team via a data transfer portal. Data management teams screen data for missingness and coherence of survey responses.

Three strategies will be employed to manage missing data. (1) A multiple imputation approach [62, 63] will involve creating multiple plausible imputations for missing covariate values, to maintain statistical power and reduce bias. (2) Inverse Probability Weighting [64, 65] will be used to adjust for the potential biases associated with non-random missingness in the outcome. (3) A missing indicator method [66, 67], where a binary indicator for missingness was included in the analyses, to directly account for the impact of missing categorical data on our study outcomes. These combined approaches will allow us to address different aspects of the missing data, ensuring a comprehensive analysis of the results.

### Outcome variables

#### Outcomes

Our primary outcomes will be clinical measures captured in the VA electronic health record, including BMI (constructed from height and weight values) and blood pressure readings (systolic and diastolic), which will be obtained from the Vital Status table in the VA Corporate Data Warehouse (CDW). In addition, HbA1c will be obtained from CDW laboratory data. A power analysis revealed that our planned sample will result in minimal detectable differences for HbA1c of 0.6 mmol/mol, for systolic blood pressure of 6.5 mm and 3.5 Hg for diastolic blood pressure, and 2.4 in BMI units (weight pounds x height inches) × 703).

We will construct healthcare cost variables from VA Managerial Cost Accounting datasets, which is an activity-based cost accounting system that maps VHA resource expenditures to individual patient encounters. Healthcare costs will be captured separately for outpatient, inpatient, emergency department, and pharmacy services. We will sum these costs for healthcare encounters occurring over the follow-up period and adjust for inflation to 2025 US dollars. Similarly, healthcare utilization will be calculated as the number of outpatient and emergency department visits, prescriptions, and inpatient days. These will serve as important secondary outcomes.

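### The power statement is wrong as printed: an HbA1c detectable difference of 0.6 does not fit mmol/mol, the BMI expression does not give BMI, and the blood pressure and BMI figures look large for 500 per group

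*Protocol article*

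**What the plan says.** The Outcomes section of the protocol article names BMI, systolic and diastolic blood pressure and HbA1c as primary outcomes taken from the electronic health record. For the planned sample it reports "minimal detectable differences for HbA1c of 0.6 mmol/mol, for systolic blood pressure of 6.5 mm and 3.5 Hg for diastolic blood pressure" and, for BMI, "2.4 in BMI units (weight pounds x height inches) × 703".

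The section on the intervention enrollment process sets the sample: "Intervention enrollment will total at least 500 (250 per site"). It gives the basis as follows: "This was derived based on a power analysis performed on the primary outcomes coupled with practical considerations", the latter being the number of Veterans the program and its services could support. It refers the reader to the outcomes section for the power analysis.

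The size of the comparison group for the record-based outcomes is not stated. The nearest figure is in the survey text after Table 2: "Potential survey participants (anticipated *n* = 1000) are mailed an opt-out letter for the survey". That pool is made up as follows: "Program enrollees and the subsample of comparison group Veterans are invited to complete a survey three times during the study". About 500 comparators is therefore an inference from the survey pool, and the full comparison group may be larger.

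**The concern.** These four figures are the article's only statement of what the study can detect on its primary outcomes, and they are offered as part of the reason for enrolling 500. Two of them cannot be taken as printed. The HbA1c value is far too small for its unit, and the BMI figure carries an expression that does not define BMI. The blood pressure unit is also broken across the two values, so neither carries mmHg.

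The three remaining figures raise a softer question: they look large for a comparison of about 500 with 500. A reader who takes the paragraph literally would credit the study with a sensitivity to HbA1c that it cannot have. The same reader might also credit it with less sensitivity to blood pressure and BMI than its size would normally give.

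**Working it through.** **Inputs from the document.** Intervention group 500. Detectable differences 0.6 mmol/mol (HbA1c), 6.5 (SBP), 3.5 (DBP) and 2.4 (BMI).

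**Assumptions, because the article does not give them.** Two-sided alpha 0.05, 80% power (90% as a variant), equal groups, and SDs of 1.2 to 2.0 percentage points for HbA1c, 15 to 20 mmHg for SBP, 9 to 12 mmHg for DBP and 5 to 8 units for BMI. One percentage point of HbA1c is 10.929 mmol/mol.

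**Formula.** MDD = (z for alpha + z for power) × SD × √(2/n), with n per group. At 80% power the z-sum is 1.960 + 0.842 = 2.802. Without the study's SDs, alpha and power the printed figures cannot be reproduced directly, so the formula is solved for the n or the SD that each would require.

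**1. HbA1c in its printed unit**
- 0.6 / 10.929 = 0.055 percentage points.
- Required n per group = 2 × (2.802 × SD / 0.6)², SD in mmol/mol. SD 1.2 points (13.1 mmol/mol) gives about 7,500; SD 2.0 points (21.9 mmol/mol) gives about 20,800.
- Conversely, at 500 per group, √(2/500) × 2.802 = 0.177, and 0.6 / 0.177 = 3.4 mmol/mol, an SD of only 0.31 percentage points.
- A larger comparison group does not rescue it. With unlimited comparators the variance is SD²/500 in place of 2 × SD²/500, so the enrollees needed only halve, to about 3,750 to 10,400.
- At 500 per group the assumed SDs give an MDD of 0.21 to 0.35 percentage points, that is, 0.21 × 10.929 = 2.3 to 0.35 × 10.929 = 3.8 mmol/mol.
- Read as percentage points, 0.6 is 0.6 × 10.929 = 6.6 mmol/mol. The other figures point the same way: if all four share one n, the n that gives an SBP SD near 18 gives an HbA1c SD near 1.7, which suits percentage points and not mmol/mol.

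**2. BMI expression**
- As printed, 200 lb and 70 in: 200 × 70 × 703 = 9,842,000.
- Weight over height squared: 200 / 70² × 703 = 28.7.
- A superscript lost in text extraction could explain the missing square, but not a multiplication sign where a division belongs.

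**3. SDs implied by the printed figures** (HbA1c read as percentage points)

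| n per group | Power | SBP | DBP | BMI | HbA1c |
|---|---|---|---|---|---|
| 500 | 80% | 36.7 | 19.8 | 13.5 | 3.4 |
| 500 | 90% | 31.7 | 17.1 | 11.7 | 2.9 |
| 250 | 80% | 25.9 | 14.0 | 9.6 | 2.4 |
| 250 | 90% | 22.4 | 12.1 | 8.3 | 2.1 |
| 125 | 80% | 18.3 | 9.9 | 6.8 | 1.7 |
| 125 | 90% | 15.9 | 8.5 | 5.9 | 1.5 |

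At 500 per group every implied SD is well above the assumed range. In the other direction, the assumed SD ranges need 63 to 185 per group at 80% power and 85 to 248 at 90%. For scale, SDs of 18, 10 and 6.5 at 500 per group and 80% power give MDDs of about 3.2 mmHg, 1.8 mmHg and 1.15 BMI units, roughly half the printed values.

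**The case against.** **The unit is a valid one.** HbA1c is properly reported in mmol/mol, so the unit itself is not impossible. This stands. The fault is that the number does not suit the unit, which is most likely a labelling slip and does not show that the underlying calculation was wrong. The printed threshold is still wrong for a primary outcome.

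**The BMI expression is only a bracketed gloss.** This also stands. The article says elsewhere that BMI is built from height and weight, and nothing suggests the data will be processed with the printed expression. It is an error of statement with no shown effect on the analysis.

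**The inverse problem has no unique answer.** Because about 125 per group makes all four SDs look ordinary, a reader might infer that the figures were computed for a quarter of the planned sample, perhaps one site's 250 split in two. The document does not support that. Alpha, power, SDs and the comparison-group size are not given, and the 250 per site are all intervention enrollees. Other assumptions work as well: with alpha split over the four measures (0.0125), 90% power and an effective 250 per group, the multiplier is (2.498 + 1.282) × √(2/250) = 0.338, and the implied SDs are 19.2, 10.4, 7.1 and 1.8. An effective 250 could come from 500 reduced by weighting and missing values.

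**HbA1c may have its own, smaller n.** The abstract mentions "e.g., HbA1c levels for patients with diabetes", but only as an example, and the outcomes section sets no such restriction. A subset could explain a larger HbA1c figure, but not the blood pressure or BMI figures, and it makes 0.6 mmol/mol still less attainable.

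**An article need not print every input.** Agreed. The absence of alpha, power and SDs is not the defect raised here; it limits how far the check can go.

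**Conclusion.** The power statement needs correction. Two points are firm. First, 0.6 mmol/mol is incompatible with a sample of about 500 per group, by a factor of roughly 15 to 42 in sample size (7,500/500 to 20,800/500) at SDs of 1.2 to 2.0 points, 80% power and two-sided 5%; 0.6 percentage points was probably meant. Second, the BMI expression does not give BMI. The split blood pressure unit is a smaller fault in the same sentence.

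The third point is weaker. For 500 per group the SBP, DBP and BMI figures imply SDs of about 37, 20 and 13.5, and HbA1c, if in percentage points, implies 3.4. They therefore look about twice as large as expected. They could reflect a smaller effective sample or a stricter alpha or power, and they cannot be reproduced or shown wrong from this document.

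A reader might also infer that the study is underpowered or that 500 was the wrong target. Neither follows. Figures larger than 500 per group requires would be conservative, and the target also rested on program capacity.

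**What to change.** Rewrite the power sentence:
- State the HbA1c figure in the unit in which it was calculated. If that was percentage points, write 0.6 percentage points (about 6.6 mmol/mol).
- Give mmHg for both pressures.
- Write BMI as weight (lb) / height (in)² × 703.
- Recheck all four figures against the group sizes used for each outcome, including the number with HbA1c values and the expected losses from weighting and missing data, and restate any that do not match. If the figures are confirmed, one clause naming the effective sample size, alpha and power behind them would resolve the apparent mismatch.

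The cost is one corrected paragraph and a short recalculation. No added patients and no change to the design are needed.

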#### Independent variables

To reduce the influence of confounding variables on our estimates, we will consider a number of measurable patient characteristics in our analyses. Demographic characteristics will include age, race, gender, marital status, priority group, insurance status, and rurality. Clinical characteristics will include the Charlson comorbidity index and the presence of mental health diagnoses. Additional information about clinical metrics and additional measures is shown in Table 2.

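### Secondary utilization and cost outcomes are called healthcare use and cost but count only VA care and VA spending, so where care is obtained cannot be separated from how much is used

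*Protocol article*

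**What the plan says.** Methods, Study design, gives as secondary outcomes: "Healthcare utilization, including primary care visits, pharmacy utilization, inpatient admissions, and ED visits". The Outcomes section takes cost from VA Managerial Cost Accounting, described as an "activity-based cost accounting system that maps VHA resource expenditures to individual patient encounters", and continues: "Similarly, healthcare utilization will be calculated as the number of outpatient and emergency department visits, prescriptions, and inpatient days".

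Other sections confirm that the source is VA alone. Implementation and effectiveness outcomes speaks of "Comparisons of health and healthcare cost outcomes derived from VA EHR data, including BMI and pharmacy utilization", and Data management places the EHR-based utilization data in the VA computing environment. No other payer's claims are named in the readable text. The survey measures in Table 3 include no item on care obtained outside VA.

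The claim is worded more broadly. The Discussion paragraph of the Abstract promises evidence on the "impact of a produce prescription program for U.S. Veterans on health outcomes, healthcare costs, and patient-reported outcomes".

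On other coverage, Independent variables states: "Demographic characteristics will include age, race, gender, marital status, priority group, insurance status, and rurality". Under Data analysis these variables enter the propensity model.

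**The concern.** The label is wider than the measurement. An emergency visit or admission paid by another insurer leaves no trace in these data, so the count models and the two-part cost models treat that Veteran as having had no such care. If both groups obtained the same share of their care in VA throughout, a rate ratio would be unaffected. If the shares differ, or move apart after enrollment, the VA-based comparison mixes two things: how much care is used and where it is obtained.

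A difference in shares is plausible here. Eligibility requires only being among "currently active patients defined by a visit to a participating VA medical center within the preceding 12 months", so some members may rely on VA only in part. The comparison group is made up of non-participants, including Veterans who declined. The program adds contact with VA staff through enrollment and then through VA classes or a dietitian consultation. At stake is whether a difference in visits or admissions can be reported as an effect on healthcare use. A shift toward VA could look like increased use or could hide a true reduction.

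**Working it through.** The plan states no figure on this point, so there is none to reproduce. The check has two parts.

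**1. Does any planned method recover outside care?**

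- *Insurance status in the propensity score* (Independent variables; Data analysis). This balances coverage at baseline. It does not measure or correct a later change in where care is obtained.
- *Multiple imputation, inverse probability weighting and missing indicators* (Data management). These act on values recognized as missing. An outside admission is not flagged as missing and enters as zero.
- *Change from baseline for secondary outcomes* (Data analysis). If applied to utilization with a pre-index period, this would cancel a stable gap in VA share on the ratio scale. It would not cancel a change in share after enrollment.
- *Subgroup analyses* (Data analysis). Those named are by benefit use, reason for non-enrollment, site and demographics. Other insurance is not among them.
- *Limitations.* The nearest sentence concerns Veterans who do not use VA regularly and so do not enter the study. It does not cover outside care by those who do enter.

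None of these closes the gap.

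**2. How large could the distortion be?**

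The document gives no share of care obtained in VA, so every share below is an assumption. Let total use be equal in both groups, with VA share s1 in enrollees and s0 in comparators.

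Apparent rate ratio = (total use × s1) / (total use × s0) = s1 / s0

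| Assumed s1 | Assumed s0 | Apparent rate ratio |
|---|---|---|
| 0.93 | 0.90 | 1.03 |
| 0.85 | 0.80 | 1.06 |
| 0.85 | 0.75 | 1.13 |

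Reversing the middle row gives 0.80/0.85 = 0.94, so the distortion can run either way. It can also mask a real effect: a true rate ratio of 0.94 multiplied by 0.85/0.80 gives 0.94 × 1.0625 = 1.00.

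To see whether shifts of this size could be declared significant, take a Wald test on the log rate ratio with negative binomial variance:

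SE² = (1/μ0 + k)/n + (1/μ1 + k)/n

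Assumptions: n = 500 per group (the document plans 500 enrollees; an equal comparison group is assumed), two-sided 0.05, 5 or 10 total visits per year, k = 0.5 or 1.0, and no precision lost to weighting. For 10 visits, k = 0.5 and shares of 0.80 and 0.85:

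- μ0 = 8.0 and μ1 = 8.5
- SE² = (0.125 + 0.5)/500 + (0.1176 + 0.5)/500 = 0.002485, so SE = 0.0499
- log(1.0625) = 0.0606, so z = 1.22 and the rejection probability is 0.229

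Over the combinations run (s0 of 0.70 or 0.80), a 5-point shift is declared significant in 14% to 28% of studies and a 10-point shift in 39% to 76%, against a nominal 5%. Weighting would lower these figures. They show what such shifts would do if they occurred, and say nothing about whether they will.

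**The case against.** The strongest reply is that the data source is disclosed and the perspective is evident. The Outcomes section names the VA cost system, the Discussion places the evidence within an integrated healthcare system, and the Conclusions aim at scale-up across VA. For a VA decision-maker, care drawn into VA is a real consequence of the program. This stands for cost: a reader might infer that the cost results are spurious, and the document does not support that. It does not rescue visits and admissions presented as healthcare use in general, because the article does not state that perspective.

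A second reply concerns the mechanism. A reader might infer that a shift into VA can happen only among enrollees. The document contradicts this. Veterans who screen positive are referred to a social worker or dietitian before any enrollment, the comparison index date itself requires a positive screen, and Limitations says that comparators may take culinary education. The main benefit is a grocery card run by an outside non-profit. What remains is a possible difference in degree.

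Third, the shares are assumed, insurance status is not defined, and Table 2, which lists metrics and measurement strategies, is not readable here and could name a further source. All of this is correct and limits the point to a risk of bias. Finally, Limitations already concedes unmeasured confounding, but that warning is general and does not tell a reader that outside care is uncounted.

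**Conclusion.** The point holds as a mismatch between label and measurement, with a risk of bias in secondary outcomes. Utilization and cost are called healthcare outcomes but capture only VA care and VHA spending, and no planned step corrects a differential or changing VA share. The risk is greatest for visits and admissions; VA cost remains a valid outcome from the VA payer's view.

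The ratios of 1.03 to 1.13 are illustrations under assumed capture shares. They should not be read as an estimate of bias in this study, since the document gives no evidence that a shift will occur, or of its size or direction. The primary clinical outcomes are outside this point. The verdict rests on the readable text and would change if Table 2 named a source of non-VA care.

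**What to change.** 1. In Study design and Outcomes, name these outcomes VA-provided utilization and VA cost, and limit conclusions to that view, including the wording in the Abstract.
2. In Data analysis, prespecify a sensitivity analysis that repeats the emergency, inpatient, outpatient and cost models in Veterans with no other recorded insurance, where VA records should be closest to complete. Report its estimate and interval beside the main result. It should not serve as a pass/fail gate, because disagreement in a smaller subset may be noise.
3. In Limitations, state that care obtained outside VA during follow-up is not counted and that the share obtained in VA may differ between groups.

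The cost is wording and one rerun of planned models, using a variable already on the covariate list, provided that it records other coverage. The downside is that the subset is smaller and its intervals wider.
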